## Abstract

**Background:**

Conventional whole brain radiotherapy (WBRT) has been established as the treatment standard in patients with cerebral metastases from small-cell lung cancer (SCLC), however, it has only modest efficacy and limited prospective data is available for WBRT as well as local treatments such as stereotactic radiosurgery (SRS).

**Methods/design:**

The present single-center prospective randomized study, conducted at Heidelberg University Hospital, compares neurocognitive function, as objectively measured by significant deterioration in Hopkins Verbal Learning Test – Revised total recall at 3 months. Fifty-six patients will be randomized to receive either SRS of all brain metastases (up to ten lesions) or WBRT. Secondary endpoints include intracranial progression (local tumor progression and number of new cerebral metastases), extracranial progression, overall survival, death due to brain metastases, local (neurological) progression-free survival, progression-free survival, changes in other cognitive performance measures, quality of life and toxicity.

**Discussion:**

Recent evidence suggests that SRS might be a promising treatment option for SCLC patients with brain metastases. The present trial is the first to prospectively investigate the treatment response, toxicity and neurocognition of WBRT and SRS in SCLC patients.

**Trial registration:**

Clinicaltrials.gov NCT03297788. Registered September 29, 2017.

**Electronic supplementary material:**

The online version of this article (10.1186/s13063-018-2745-x) contains supplementary material, which is available to authorized users.

## Background

Patients suffering from small cell lung cancer (SCLC) are at high risk for developing brain metastases (BM) during the course of their disease. Between 40% and 50% of patients develop BM until time of death [1] and the risk of developing BM further increases with prolonged survival [2]. Prophylactic cranial irradiation (PCI) is offered to limited disease patients if they respond to first line regime [3–5]. However, up to 10–15% of patients present with BM at initial diagnosis [6–8], and if magnetic resonance imaging (MRI) is used as a diagnostic tool for initial staging, the proportion increases to 15–20% [9]. Treatment options are usually limited to whole brain radiotherapy (WBRT) and palliative chemotherapy [10]. The actual effect of therapeutic WBRT has mainly been studied in small retrospective and non-randomized studies [2, 11–15]. Moreover, patients within recursive partitioning analysis (RPA) class III were commonly excluded from any prospective BM trials that involved WBRT [16, 17]. In a recent Japanese trial, prophylactic cranial irradiation did not result in longer overall survival compared with observation plus regular MRI follow-ups in patients with extensive disease (ED) SCLC [18]. PCI is therefore no longer recommended for patients with ED SCLC [19] when patients undergo regular MRI brain scans during follow-up [18]. Therefore, the number of patients with oligometastasic cerebral disease might rise.

The present trial aims to investigate the treatment response to ‘conventional whole brain radiotherapy’ and ‘stereotactic radiotherapy’ (SRS) in SCLC patients. The primarily investigated endpoint is neurocognitive function, as objectively measured by significant deterioration in Hopkins Verbal Learning Test – Revised (HVLT-R) total recall at 3 months [20]. Secondary endpoints include intracranial progression (local tumor progression, number of new cerebral metastases), extracranial progression, overall survival, death due to brain metastases, local (neurological) progression-free survival, progression-free survival, changes in other cognitive performance measures, quality of life, and toxicity.

## Methods/design

The study is a randomized phase II study with two study arms. The standard arm is WBRT and the experimental arm is SRS (Fig. 1). We hypothesized that patients treated with WBRT would have inferior neurocognitive function based on the HVLT-R [20] compared with patients treated with SRS alone.

**Fig. 1 Fig1:**
[figure not shown]
Intervention and assessment schedule for the ENCEPHALON trial

### Recruitment and randomization

Eligible patients who present at the Departments of Radiation Oncology, University Hospital Heidelberg, Germany, will be recruited to the study. Eligibility requirements are:

### Inclusion criteria

Histologically confirmed ED SCLCMRI-confirmed cerebral metastasis (not resected, maximum number of 10)Age ≥ 18 years of ageFor women with childbearing potential (and men), adequate contraceptionAbility of subject to understand character and individual consequences of the clinical trialWritten informed consent (must be available before enrolment in the trial)

### Exclusion criteria

Refusal of the patients to take part in the studyPrevious radiotherapy of the brainPatients who have not yet recovered from acute high-grade toxicities of prior therapiesKnown carcinoma < 5 years ago (excluding carcinoma in situ of the cervix, basal cell carcinoma, squamous cell carcinoma of the skin) requiring immediate treatment interfering with study therapyPregnant or lactating womenParticipation in another clinical study or observation period of competing trials, respectivelyMRI contraindication (i.e., cardiac pacemaker, implanted defibrillator, certain cardiac valve replacements, certain metal implants)Karnofsky Performance Score < 60Simultaneous cytotoxic chemotherapyLast application of chemotherapy/immunotherapy/targeted therapy < 1 week before cerebral radiotherapy

After meeting eligibility criteria, 56 patients will be randomly assigned to SRS or WBRT. To achieve comparable intervention groups, patients will be allocated in a concealed fashion in a 1:1 ratio by means of randomization using a centralized web-based tool (www.randomizer.at). Randomization will be stratified with respect to time of appearance (synchronous vs. metachronous). Block randomization with varying block lengths will be performed to achieve equal group sizes in total. BM are defined as synchronous if discovered at the time of initial diagnosis of the primary tumor or within 3 months thereafter. All other patients will be classified as metachronous.

### Assessment of the primary and secondary endpoints

The primary endpoint is neurocognition after cerebral irradiation in SCLC patients treated with WBRT or SRS, defined as a drop of at least 5 points from baseline in HVLT-R total recall at 3 months. Secondary objectives are intracranial progression (local tumor progression, number of new cerebral metastases), extracranial progression, overall survival, death due to brain metastases, local progression-free survival, progression-free survival, changes in other cognitive performance measures, quality of life, and toxicity.

Time to progression is defined as the number of days from randomization to the first occurrence of the respective event. Overall survival time is defined as number of days from randomization until death or end of follow-up. For patients alive at the end of the study, the overall survival time will be censored at the time of the last visit or follow-up contact.

Time to death due to BM is defined as number of days from randomization until death due to BM or end of follow-up, where death due to BM is defined as death with intracranial progression as a component of cause of death. Locally progression-free survival time is defined as number of days from randomization until local tumor progression, death without prior local progression, or end of follow-up. The occurring events of interest will be classified as (1) progression of cerebral metastases present at baseline only, (2) occurrence of new cerebral metastases only, (3) simultaneous detection of progression of cerebral metastases present at baseline and of new metastases, and (4) death without local progression.

Time to extracranial progression is defined as number of days from randomization until extracranial progression or end of follow-up, where extracranial progression is the first date on which progressive disease outside the brain occurred according to the physician treating the primary disease. Progression-free survival time is defined as number of days from randomization until the first occurrence of intracranial or extracranial progression, death without prior progression, or end of follow-up. Intracranial progression is defined as occurrence of progressive disease concerning the pre-existing BM or the occurrence of new BM.

Local tumor progression (progressive disease, PD) is defined as occurrence of intracranial progression) in the area of the SRS.

### Radiotherapy

#### Treatment planning for WBRT

For WBRT, patients will be immobilized using an individually manufactured head mask. For treatment planning, computed tomography (CT) without contrast, contrast-enhanced CT as well as MRI will be performed for optimal target definition. The target volume includes the whole brain. WBRT will be delivered by opposed lateral 6 MeV photon beams. Dose constraints of normal tissue will be respected according to QUANTEC reports [23, 24]. WBRT will be applied in 10 once-daily fractions each of 3 Gy, to a total dose of 30 Gy in 10 fractions to the whole brain.

#### Treatment planning for SRS

MRI and CT imaging are 3-dimensionally fused using a validated non-elastic imaging fusion algorithm and the fusion results are cross-checked by an experienced physician and adapted if necessary.

Organs at risk are contoured and adapted on the basis of CT scans and MRI. For target delineation, a gross target volume (GTV) and a planning target volume (PTV) are contoured. The basis for GTV definition is the contrast-based, T1-weighted, three-dimensional MPRAGE sequence. The GTV consists of all contrast-enhanced tissue associated with the target lesion and all additional tissue judged by an experienced physician to be part of the suspect target lesion (e.g. non-contrast-enhanced necrotic tissue within or adjoining cystic metastatic lesions). To the GTV, a PTV margin of 1 mm is added by isotropic expansion that can be slightly modified if deemed necessary by the treating physician (e.g., intersection with adjoining organs at risk).

Treatment planning for SRS will be performed using Accuray’s Multiplan or subsequent approved treatment planning systems for CyberKnife^®^.

SRS will be applied in one to a maximum of six fractions. For SRS, the dose prescription to the PTV will be as follows (risk adapted SRS dose prescription volume and location based):20 Gy to the 70%-isodose (lesions < 2 cm max. diameter)18 Gy to the 70%-isodose (lesions 2–3 cm max. diameter)6 × 5 Gy to the conformally surrounding isodose (lesions > 3 cm max. diameter or brain stem)

Dose constraints of normal tissue will be respected according to QUANTEC reports [23, 24] and extensive clinical experience at our institution.

### Statistical analysis

The primary hypothesis of the trial is that there is a difference between the two treatment arms with respect to the primary endpoint, defined as a drop of at least 5 points from baseline in HVLT-R total recall at 3 months after baseline (T0). Chang et al. [25] observed deterioration probabilities of 0.64 for SRS + WBRT and 0.20 for SRS alone at 4 months after baseline. Based on those results, assuming a deterioration probability of 0.20 for the SRS arm and 0.64 for the WBRT arm in our trial, *n* = 19 patients per arm are required to demonstrate a difference between treatment arms applying a χ^2^ test at a two-sided significance level of α = 0.05 with a probability of 1–β = 0.8. Assuming exponentially distributed survival times with a median of 6 months for both groups, 29.3% of all randomized patients are expected to have died before the measurement of the primary endpoint. Thus, *n* = 28 patients per group are required to yield a sufficiently high power for a comparison of the deterioration rate within the two groups. Statistical analysis is based on the International Conference on Harmonization Guidelines Structure and Content of Clinical Study Reports and Statistical Principles for Clinical Trials. A detailed methodology for the statistical analysis will be described in the statistical analysis plan, which will be finalized before database lock. Statistical analysis will be performed using SAS v9.4 or higher.

### Efficacy evaluation

The primary hypothesis of the trial is that there is a difference between the two treatment arms with respect to the primary endpoint, defined as a drop of at least 5 points from baseline in HVLT-R total recall at 3 months. With π_SRS_ being the deterioration probability in the SRS arm and π_WBRT_ being the deterioration probability in the WBRT arm, the null hypothesis H_0_: π_SRS_ = π_WBRT_ is tested against its alternative H_1_: π_SRS_ ≠ π_WBRT_ at a two-sided significance level of α = 0.05 using a Cochran–Mantel–Haenszel test adjusting for the confounder time of appearance (synchronous vs. metachronous). Missing data for the primary outcome variable will be replaced by using multiple imputation which takes the covariates of treatment group, time of appearance (synchronous vs. metachronous), and the baseline HVLT-R total recall score into account by application of the fully conditional specification method [26]. For the secondary time-to-event endpoints overall survival, local progression-free survival, and locoregional progression-free survival, median event times and 1-year rates will be given with 95% confidence intervals and Kaplan–Meier curves will be calculated for both treatment groups. A (descriptive) log-rank test stratified for time of appearance (synchronous vs. metachronous) will be performed in order to assess differences between the two treatment groups, and a descriptive *P* value will be given. A Cox proportional hazard model with overall survival as dependent variables well as treatment group and time of appearance as independent factors will be fitted to estimate the hazard ratio for the treatment group together with a 95% confidence interval.

All further secondary outcomes will be analyzed descriptively, and descriptive *P* values will be reported together with corresponding 95% confidence intervals.

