## Discussion

The primary aim of this trial is to exploratively investigate the effect of SRS compared to WBRT in patients with BM from SCLC. Currently, according to national guidelines, the recommendation for patients with BM from SCLC, regardless of the number of BM, is WBRT [10]. The actual evidence behind those recommendations is low and mainly based on retrospective studies from the last three decades and is analogically reasoned by previous PCI studies [3–6, 27]. In a recent Japanese trial, prophylactic cranial irradiation did not result in longer overall survival compared with observation in patients with ED SCLC and PCI is therefore no longer recommended for patients with extensive disease SCLC when patients receive regular MRI examinations during follow-up. Furthermore, if SCLC patients are regularly checked with MRI, the actual number of patients with limited number of BM might rise. The general use of WBRT in SCLC patients is additionally supported by the general paradigm of a diffuse intracranial disease pattern; even so, these beliefs derive from a pre-MRI era. The EORTC conducted a prospective, phase II study between 1989 and 1995 that included patients (*n* = 22) with brain-only metastases SCLC to evaluate the efficacy of WBRT [28]. The median response duration in patients with an objective response was 5.4 months, and the median survival of all patients was 4.7 months. A number of retrospective studies investigated prognostic factors and identified subgroups of SCLC patients with a favorable prognosis [15, 29–31]. In a recent report [5], we investigated 229 SCLC patients with BM from SCLC; median overall survival after WBRT was 6 months. The main prognostic factors associated with overall survival were performance status, time of appearance of intracranial disease (synchronous vs. metachronous), initial response to chemotherapy, and higher RPA class. Interestingly, patients in RPA class I showed a median survival after WBRT of 17 months and had a comparable outcome to patients with non-cerebral disease treated with PCI. Furthermore, 39% of patients had 1–5 BM and the majority of patients received staging with cerebral MRI prior to treatment [32]. The recently developed disease-specific prognostic score for patients with BM from SCLC was even more prognostic than RPA score and diagnosis-specific graded prognostic assessment score [29] and revealed a subgroup of patients with a very short survival (class I) and a subgroup with a favorable prognosis (class II) [33]. The disease-specific prognostic score for patients with BM from SCLC will be validated within the ENCEPHALON trial. Because of the multiple prognostic factors and differences in outcomes in patients with BM from SCLC, a one- fits-all treatment framework, in which all patients are automatically recommended for WBRT, is no longer appropriate and the actual evidence for this recommendation is missing.

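### The overall-survival Cox model is valid but leaves out Karnofsky score, a recorded main prognostic factor: a modest missed efficiency gain, not a bias

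*Protocol article*

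**What the plan says.** The Efficacy evaluation section of the protocol article fits a Cox model for overall survival in which "treatment group and time of appearance as independent factors will be fitted to estimate the hazard ratio", with a 95% confidence interval. The accompanying survival test is secondary: "A (descriptive) log-rank test stratified for time of appearance (synchronous vs. metachronous) will be performed".

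The paragraph after the exclusion criteria sets the design: "56 patients will be randomly assigned to SRS or WBRT", and "patients will be allocated in a concealed fashion in a 1:1 ratio". It names one stratification factor: "Randomization will be stratified with respect to time of appearance (synchronous vs. metachronous"). The exclusion list bars a Karnofsky score below 60, so the score has to be established for each patient before enrolment.

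The Discussion reports a series of 229 patients with brain metastases from small-cell lung cancer: "The main prognostic factors associated with overall survival were performance status, time of appearance of intracranial disease", followed by initial response to chemotherapy and RPA class.

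**The concern.** The model includes the second-named prognostic factor, which is also the stratum, and omits the first, although a measure of it is on file for every patient. Stratification does not balance Karnofsky score, so with 28 patients per arm its distribution is left to chance.

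Two things follow if the factor is strong. In a Cox model, omitting a strong prognostic variable pulls the treatment hazard ratio towards 1 when there is a real effect. And if the baseline table shows a visible imbalance, readers will ask for an adjusted estimate; one produced only then would be data-driven. The article asks this model for an estimate with an interval, so the quality of estimation matters even though the comparison is descriptive.

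**Working it through.** **Inputs from the article.** 56 patients, 1:1, so 28 per arm. On survival, the Statistical analysis section writes: "Assuming exponentially distributed survival times with a median of 6 months for both groups". Follow-up within the trial is 12 months.

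**The article's own survival figure.** Deaths before 3 months: 1 − 0.5^(3/6) = 0.293, which is the stated 29.3%. The article gives no event number or power for overall survival.

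**Expected deaths and precision at 12 months.**
- Equal survival: 56 × (1 − 0.5^(12/6)) = 56 × 0.75 = 42 deaths.
- SE(log HR) ≈ 2/√42 = 0.309. The 95% interval runs from the hazard ratio divided by 1.83 to the hazard ratio multiplied by 1.83, since exp(1.96 × 0.309) = 1.83.
- If the true hazard ratio were 0.60 for SRS: 28 × 0.75 + 28 × (1 − 0.5^1.2) = 21.0 + 15.8 ≈ 37 deaths.

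**Assumptions not in the article.** Half the patients in the lower Karnofsky group; hazard ratio for that group 1.5, 2 or 3; time of appearance split 50:50 with hazard ratio 1.5.

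**Chance imbalance.** The SD of the between-arm difference in the share with lower Karnofsky is √(0.5 × 0.5 × 2/28) = 0.134, about 13 percentage points. In simulation a difference of 20 percentage points or more occurred in about 14% of trials. At a true hazard ratio of 1, the log hazard ratio moved by 0.43, 0.69 or 1.12 per unit of imbalance (Karnofsky HR 1.5, 2, 3). A 20-point difference therefore shifts the estimate by exp(0.2 × 0.43) = 1.09, exp(0.2 × 0.69) = 1.15 or exp(0.2 × 1.12) = 1.25.

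**Cox simulation.** 28 vs 28, 12 months of follow-up, 4,000 trials per setting, both models fitted to the same trials. Allocation was simple 28:28, not stratified.

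| Karnofsky HR | True treatment HR | Mean HR, stated model | Mean HR, plus Karnofsky | Rejection, stated | Rejection, plus Karnofsky |
|---|---|---|---|---|---|
| 1.5 | 1.0 | 1.002 | 1.002 | 6.1% | 6.0% |
| 2 | 1.0 | 1.002 | 1.001 | 5.3% | 6.0% |
| 3 | 1.0 | 1.004 | 1.008 | 5.5% | 5.4% |
| 1.5 | 0.6 | 0.597 | 0.587 | 32.2% | 32.9% |
| 2 | 0.6 | 0.605 | 0.585 | 29.9% | 32.0% |
| 3 | 0.6 | 0.635 | 0.587 | 25.1% | 31.6% |

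Coverage of the 95% interval over the six settings was 93.9–94.8% for the stated model and 93.8–94.6% with Karnofsky added. The power differences are 0.7, 2.1 and 6.5 points. The Monte Carlo standard error of one rejection rate near 30% is √(0.3 × 0.7/4000) = 0.7 points, so the gain at Karnofsky HR 1.5 is close to nothing. The adjusted log hazard ratio is slightly more variable (for example SD 0.341 against 0.328 at Karnofsky HR 2 and no effect). The gain therefore comes from less attenuation, not from a narrower interval.

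**Given a visible imbalance.** Take trials where 20 percentage points or more fall against SRS (7–8% of trials), with true hazard ratio 0.60 and Karnofsky HR 2 / 3. The stated model averages about 0.75 / 0.84 with coverage of about 89% / 84%. The adjusted model averages about 0.60 / 0.59 with coverage of about 92% / 93%. These figures rest on a few hundred simulated trials each.

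**The case against.** The strongest objection is that nothing here is wrong. Time of appearance is the only stratum, and the Cochran–Mantel–Haenszel test, the log-rank test and the Cox model all use it. Adjusting for the stratification factor is standard and coherent. Overall survival is secondary, its test is descriptive, no sample size rests on it, and power stays around 25–33% with either model. All of this stands.

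A reader might go further and infer that chance imbalance biases the hazard ratio or invalidates the comparison. The article does not support that. Allocation is concealed and random, so over repeated trials the imbalance is random error, which the interval already covers. The shifts of 1.09 to 1.25 also lie well inside the interval factor of 1.83. A reader might also treat overall survival as the formal check that omitting WBRT does no harm; the article lists it among many secondary endpoints and gives it no such role.

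Three further points limit the size. The article gives neither a Karnofsky distribution nor a prognostic hazard ratio. Excluding scores below 60 may narrow the contrast among enrolled patients. And the Discussion names other factors and a prognostic score as well; Karnofsky is singled out because the eligibility rule guarantees that it is known for everyone.

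A supportive adjusted model may sit in the statistical analysis plan, which is not at hand. But the article states this model explicitly and does not leave its covariates open.

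**Conclusion.** The stated model is valid. Leaving out Karnofsky score is a missed efficiency gain and leaves no prespecified answer to a visible imbalance; it is neither a bias across repeated trials nor a type I error problem. The attenuation of a true 0.60 (to 0.635 at most in the simulation) and the power cost of roughly 1 to 7 points hold under a 50:50 Karnofsky split, a prognostic hazard ratio of 1.5 to 3, and 12 months of follow-up. At the weak end of that range the loss is negligible. The case for the covariate is clearest in the minority of trials with a marked imbalance, where the adjusted estimate stays closer to the truth. This is a minor, optional improvement to a secondary analysis.

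**What to change.** Before data are seen, add baseline Karnofsky score to the overall-survival Cox model as a prespecified covariate, for example as a linear term per 10 points, and report the currently stated model alongside it. The statistical analysis plan is to be finalised before database lock, so it can carry the change. The stratified log-rank test can stay as it is.

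The cost is one more parameter with about 42 expected deaths (about 37 if the true hazard ratio is 0.60), which is affordable. The interval will be no narrower, and may be slightly wider. The adjusted hazard ratio is conditional on Karnofsky score, so the two estimates can differ without any error and the report should say so. No new data are needed, and the sample size and primary analysis are untouched.
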